## Procedures for handling dropouts

Investigators will make an attempt to contact those subjects who do not return for scheduled visits or follow-up. Information gathered will be described on the Study Conclusion page of the CRF and on Medication/Adverse event forms.

## 9.3 Reasons for dropout

It will be specified on the Study Conclusion page of the CRF, which of the following possible reasons were responsible for dropout of the subject from the study:

- Serious adverse event
- Non-serious adverse event
- Protocol violation (specify)
- Consent withdrawal, not due to an adverse event
- Migrated/moved from the study area
- Lost to follow-up
- Other (specify)

# DATA EVALUATION: CRITERIA FOR EVALUATION OF OBJECTIVES

## Study Objectives

# Primary Objective

Assess the safety and reactogenicity of FMP010/AS01B candidate malaria vaccine in healthy malaria-naïve adults from the US and malaria experienced adults in Kenya.

# Secondary Objective

Measure and compare, by Growth Inhibition Assay (GIA), the functional humoral immune responses induced in malaria experienced adults in Kenya to that induced in healthy malaria-naïve adults from the US by FMP010/AS01B and FMP1/AS02 A.

**Tertiary Objectives**

Measure and compare, by enzyme-linked immunoabsorbent assay (ELISA), the humoral immune responses induced by vaccine candidate FMP010/AS01B in malaria experienced adults in Kenya to those induced in healthy malaria-naïve adults from the US.

## Study Endpoints

**Co-primary endpoints**

- Occurrence and intensity of solicited symptoms on day of vaccination plus days 1, 2, 3 and 7 and after each vaccination
- Occurrence and intensity of unsolicited symptoms over a 30-day follow-up period (day of vaccination plus 29 subsequent days) after each vaccination
- Occurrence of serious adverse events (SAEs), defined IAW 21 CFR 312.32(a), during the study period.

**Secondary endpoints**

Functionality of antibodies elicited as measured by percent parasite growth inhibition determined by GIA against FVO and 3D7 *P. falciparum* strains at specified time points

**Tertiary endpoints**

Titers of anti-FMP010 and anti-FMP1 antibodies as determined by ELISA at specified time points

- To whole MSP142 antigen of 3D7 and FVO allele

● To subunit antigens and selected peptides of MSP142 molecule

## Exploratory Endpoints

These assays may provide additional information on the immunogenicity of the vaccine candidate FMP010/AS01B. The assays will be completed at both WRAIR and USAMRU-K if, after performing endpoint assays, sufficient sample remains and study priorities permit.

- Detection of *P. falciparum* antigens by HRP-2 and pLDH ELISAs
- Growth Inhibition Assays (GIAs) in immunized malaria-experienced Kenyan adults
- Titers of anti-FMP010 and FMP1 antibodies as determined by bead-based flow cytometric assays (*Luminex™*) at specified time points
- Anti-merozoite immunofluorescence (IFA) assays to assess ability of antibodies to recognize MSP1 molecule on infected erythrocytes
- Processing inhibition assay (PIA) to assess ability of antibodies to inhibit processing of MSP142 molecule to MSP133 and MSP119
- Cytokine bead-based flow cytometric assay (*Luminex*) to assess cytokine production in responses to vaccine administration
- Assays such as ELISPOT and intracellular cytokine staining to assess cellular immune responses

##

## Study data sets to be evaluated

**Total Vaccinated Cohort**

The Total Vaccinated Cohort will include all vaccinated subjects for whom data are available. Thus, the total analysis of safety will include all subjects with at least one vaccine administration documented and the total analysis of immunogenicity will include vaccinated subjects for whom data concerning immunogenicity endpoint measures are available. The Total Vaccinated Cohort analysis will be performed per treatment actually administered.

**Protocol defined or According To Protocol (ATP) cohort for analysis of safety**

The ATP cohort for analysis of safety/reactogenicity will include all subjects who meet all eligibility criteria and comply with all procedures defined in the protocol and will include subjects for whom data are available for the analysis of safety/reactogenicity.

The ATP cohort for analysis of safety will include all evaluable subjects

- who have received at least one dose of study vaccine according to their random assignment;
- who have sufficient data to perform an analysis of safety (at least one vaccine dose with safety follow-up);
- who have not received a vaccine not specified or forbidden in the protocol and for whom elimination criteria were not applied; and,
- for whom the randomization code has not been broken (as applicable).

**Protocol defined or ATP cohort for analysis of immunogenicity**

The ATP cohort for analysis of immunogenicity will include all subjects for whom differential treatment effect on immunogenicity is likely (i.e., those meeting all eligibility criteria, complying with the procedures defined in the protocol) and will include subjects for whom assay results are available for antibodies against at least one study vaccine antigen component after vaccination.

##

## Estimated Sample Size and Sample Size Justification

This study is designed to assess the initial safety and immunogenicity of a new candidate malaria vaccine. The sample size is in keeping with small numbers of volunteers traditionally included in initial Phase I studies. Comparative statistics will be performed but will have low power to detect other than very large differences between groups therefore the most likely result will be a descriptive analysis of safety.

## Final Analyses

###

### Analysis of demographics

Demographic characteristics (age, sex, and race) of each study cohort will be tabulated. The mean age (plus range and standard deviation) by sex of the enrolled subjects, as a whole, and per group, will be calculated.

### Analysis of safety

**Analysis of reactogenicity**

Reactogenicity analyses will be analyzed as follows.

- The overall percentage of subjects with at least one local adverse event (solicited and unsolicited), with at least one general adverse event (solicited and unsolicited), during the seven-day follow-up period after vaccination will be tabulated.
- The incidence, intensity and relationship of individual solicited symptoms over the 7-day follow‑up period will be calculated per group and vaccine dose.
- The number of subjects with at least one report of an unsolicited adverse event, classified by WHO Preferred terms or by the Medical Dictionary for Regulatory Activities (MedDRA) if available and reported after the Vaccination Phase, will be tabulated per group and vaccine dose. The intensity and relationship to vaccination of the unsolicited symptoms reported will also be assessed. Serious adverse events are expected to be rare, but where observed will be described.

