**Part B: Phase 1b Double-blind Controlled at USAMRU-K in Western Kenya**

Healthy, malaria-experienced adults aged 18-50 years

Two groups (20 volunteers in Group 3, 10 volunteers in Group 4; 30 volunteers total)

- Group 3 will receive full dose FMP010 antigen (approximately 50 µg) in 0.5 mL AS01B adjuvant
- Group 4 will receive the licensed rabies vaccine Rabipur® (manufactured in India by Chiron Behring Vaccines Pvt, Ltd) supplied in single dose vials containing lyophilized antigen with 1.0 mL of diluent (sterile water) for injection.

Vaccination schedule of 0, 28 ± 3 days and 56 days ± 3 days

Intramuscular route of administration in the deltoid muscle of the non-dominant arm

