## 5.5 Outline of study procedures

### Screening and Vaccination phase

All subjects enrolled in the study will be issued an emergency notification card that details their participation in the study and specific contact phone numbers of the investigators. Vitals signs (temperature, pulse, blood pressure) are recorded at all scheduled study visits unless indicated otherwise.

The schedule below applies to Part B of the protocol and the Day numbers refer to volunteer day of study not study date.

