**Visit 21: Day 112 (± 7 days) – Final Study visit**

- Check elimination criteria; record medications
- History and directed physical examination
- Record any unsolicited adverse events occurring after the last vaccine dose
- Collection of urine for pregnancy tests where applicable
- Blood collection - whole venous blood will be collected:

**Part B (Kenya):** Approximately 11 mL whole venous blood will be collected for:

- - 5 mL for a CBC, creatinine ALT, and AST.
  - 5 mL for humoral immune studies. The research samples will be centrifuged and the serum stored at ‑20°C (± 5°) or colder until processing.
  - 1 mL for *P. falciparum* antigens detection by HRP 2 and pLDH ELISAs

Table 2: Time and event Schedule for Groups 3 & 4

| **Part B (Kenya): Vaccination Phase** | **Screen** |  | | |  | | |  | | |  | | | | | | | |
| --- | --- | --- | --- | --- | --- | --- | --- | --- | --- | --- | --- | --- | --- | --- | --- | --- | --- | --- |
| Day | -60 to -1 | 0 | 1-6 | 7 | | 14 | 28 | | 29-34 | 35 | | 42 | 56 | 57-62 | 63 | 70 | 86 | 112 |
| Visit | 1 | 2 | 3-5 | 6 | | 7 | 8 | | 9-11 | 12 | | 13 | 14 | 15-17 | 18 | 19 | 20 | 21 |
| **Vaccination with FMP010 / AS01B or *Rabipur*** |  | **1** |  |  | |  | **2** | |  |  | |  | **3** |  |  |  |  |  |
| Screening |  |  |  |  | |  |  | |  |  | |  |  |  |  |  |  |  |
| Briefing |  |  |  |  | |  |  | |  |  | |  |  |  |  |  |  |  |
| Informed consent – for study and HIV (part B – Kenya) testing |  |  |  |  | |  |  | |  |  | |  |  |  |  |  |  |  |
| Comprehension Assessment |  |  |  |  | |  |  | |  |  | |  |  |  |  |  |  |  |
| Check of inclusion criteria |  |  |  |  | |  |  | |  |  | |  |  |  |  |  |  |  |
| Check of exclusion criteria |  |  |  |  | |  |  | |  |  | |  |  |  |  |  |  |  |
| Medical history |  |  |  |  | |  |  | |  |  | |  |  |  |  |  |  |  |
| Physical examination |  |  |  |  | |  |  | |  |  | |  |  |  |  |  |  |  |
| **Vaccination** |  |  |  |  | |  |  | |  |  | |  |  |  |  |  |  |  |
| Pre-vaccination assessment |  |  |  |  | |  |  | |  |  | |  |  |  |  |  |  |  |
| Post-vaccination assessment |  |  |  |  | |  |  | |  |  | |  |  |  |  |  |  |  |
| **Follow-up visit** |  |  |  |  | |  |  | |  |  | |  |  |  |  |  |  |  |
| Check elimination criteria and record medications |  |  |  |  | |  |  | |  |  | |  |  |  |  |  |  |  |
| Recording of unsolicited adverse events |  |  |  |  | |  |  | |  |  | |  |  |  |  |  |  |  |

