Although not considered as an adverse event, hospitalization for either elective surgery related to a pre-existing condition that did not increase in severity or frequency following initiation of the study, or for routine clinical procedures (including hospitalization for “social” reasons) that are not the result of an adverse event, must be recorded in the CRF. If the hospitalization arises from a pre-existing condition, or was planned prior to the first vaccination, it should be recorded in the Medical History form of the CRF. If the hospitalization arises from a pre-existing condition, and the hospitalization was planned after the first vaccination, it should be recorded in the adverse event page of the CRF. In both cases, it should be recorded as ‘Hospitalization,’ and the relationship to vaccination will be checked “No.”

*Surveillance period for occurrence of adverse events*

All adverse events occurring within one month (minimum 30 days) following administration of each vaccine must be recorded on the Adverse Event form in the participant's CRF, irrespective of severity or whether or not they are considered vaccination-related. See Section 8.5 for instructions for recording and reporting of serious adverse events.

*Recording adverse events*

At each visit/assessment, all adverse events either observed by the investigator or one of his clinical collaborators or reported by the participant spontaneously or in response to a direct question will be evaluated by the investigator. Adverse events not previously documented in the study will be recorded in the Adverse Event form within the participant's CRF. The nature of each event, date and time (where appropriate) of onset, outcome, intensity, and relationship to vaccination should be established. Details of any corrective treatment should be recorded on the appropriate page of the CRF.

Adverse events already documented in the CRF, i.e. at a previous assessment, and designated as ‘ongoing’ should be reviewed at subsequent visits, as necessary. If these have resolved, the documentation in the CRF should be completed.

N.B. If an adverse event changes in frequency or intensity during a study period, the highest intensity will be recorded. If the adverse event recurs with a defined interval of symptom-free time (>24 hours) in between episodes, new record of the event will be started.

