### Unsolicited adverse events

Unsolicited symptoms are adverse events reported by the subjects which are different from those solicited or solicited symptoms which begin after the seven-day follow-up period for solicited symptoms. Space on the diary cards/source documents and CRF will be allocated for the recording of unsolicited symptoms. Should any systemic (general) signs/symptoms be reported, their relationship with the study vaccine will be assessed by the Investigator and transcribed into the CRF, as described in section 8.3.

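### The unsolicited-event table in Section 10.4.2 is restricted to events reported after the Vaccination Phase, which contradicts the 30-days-after-each-dose co-primary endpoint and cannot give the per-dose table it asks for

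*Protocol*

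**What the plan says.** **Endpoint.** The second co-primary endpoint, stated in the Protocol synopsis and in Sections 2.2 and 10.2, is "Occurrence and intensity of unsolicited symptoms over a 30-day follow-up period (day of vaccination plus 29 subsequent days) after each vaccination".

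**Collection.** Section 8.1.1 supports that endpoint: "All adverse events occurring within one month (minimum 30 days) following administration of each vaccine must be recorded".

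**Analysis.** In Section 10.4.2, Analysis of reactogenicity, the third bullet is the only one devoted to unsolicited events. It counts subjects with at least one such event "reported after the Vaccination Phase, will be tabulated per group and vaccine dose". It mentions no 30-day window. The first bullet of that section also includes unsolicited events, but pooled with solicited ones and only for the seven days after vaccination.

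**The phase.** No sentence defines where the Vaccination Phase ends. The label appears in the Section 5.5 heading, "Screening and Vaccination phase", under which all 21 visits are listed. It appears again in the header of Tables 2 and 3, "Part B (Kenya): Vaccination Phase", above columns that run to the last visit, "Visit 21: Day 112 (± 7 days) – Final Study visit".

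**Schedule.** "Vaccination schedule of 0, 28 ± 3 days and 56 days ± 3 days".

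**The concern.** The endpoint looks forward from each dose. The analysis sentence looks only at what comes after a phase that contains all three doses. The two cannot both be followed, and the analysis sentence also contradicts itself: events confined to the time after the phase cannot be broken down by Doses 1, 2 and 3.

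This is more than a detail left open for a statistical analysis plan, because the protocol states a restriction. A plan that copied it would lose most or all of a co-primary safety endpoint. A plan that ignored it would depart from the protocol. The sample-size section expects a mainly descriptive safety analysis, so tables of this kind are the principal output of the trial.

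A smaller matter comes with it. The 30-day window is longer than the nominal 28-day interval between doses. Once the restriction is removed, a per-dose table needs to say where an event in the overlap is counted.

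**Working it through.** **Inputs.** Doses at Days 0, 28 ± 3 and 56 ± 3 (synopsis). Window per dose: vaccination day plus 29 days (Section 10.2). Final visit: Day 112 ± 7 (Section 5.5).

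**Step 1: reproduce the stated window.** 1 + 29 = 30 days. A dose on Day d has the window Day d to Day d + 29. On the nominal schedule:

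- Dose 1: Days 0–29
- Dose 2: Days 28–57
- Dose 3: Days 56–85

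Together these cover Days 0–85, which is 86 distinct days.

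**Step 2: days that survive the restriction.** Count the window days falling strictly after the end of the phase, for each candidate end. This assumes that an event is reported on or close to its day of onset.

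| End of phase | Dose 1 | Dose 2 | Dose 3 | Distinct days |
|---|---|---|---|---|
| Day 112 (Table 2–3 headers) | 0/30 | 0/30 | 0/30 | 0/86 |
| Day 105 (earliest final visit, 112 − 7) | 0/30 | 0/30 | 0/30 | 0/86 |
| Day 86 (30-day visit after Dose 3) | 0/30 | 0/30 | 0/30 | 0/86 |
| Day 63 (7-day visit after Dose 3) | 0/30 | 0/30 | 22/30 | 22/86 |
| Day 56 (Dose 3) | 0/30 | 1/30 | 29/30 | 29/86 |

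In the last row, Days 57–85 remain: 85 − 57 + 1 = 29 days, and 29/86 is about 34%. The single Dose 2 day is Day 57. Dose 1 contributes nothing in any row.

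**Step 3: overlap with the next dose.** If a dose is given on Day a and the next on Day b, the overlap is max(0, a + 30 − b) days.

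- Nominal: 0 + 30 − 28 = 2 days (Days 28–29), and 28 + 30 − 56 = 2 days (Days 56–57).
- Dose 1 to 2, with Dose 2 on Days 25, 26, 27, 28, 29, 30, 31: overlap 5, 4, 3, 2, 1, 0, 0 days.
- Dose 2 to 3, largest (Days 31 and 53): 31 + 30 − 53 = 8 days. Of the 7 × 7 = 49 allowed combinations, 34 overlap.
- At the other extreme there are gaps that belong to no window: one day (Day 30) if Dose 2 falls on Day 31, and four days (Days 55–58) if Doses 2 and 3 fall on Days 25 and 59.

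**Step 4: after correction.** With the restriction removed, all 86 nominal days enter the analysis. With each event counted under the most recent dose, the nominal days divide into 0–27, 28–55 and 56–85: 28 + 28 + 30 = 86, with none counted twice.

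**The case against.** The phrase is probably a slip. The same sentence asks for results by dose, which shows what was intended, and all events are recorded for at least 30 days after each dose, so the data will exist. That stands, and it is why the correction is cheap. It does not make the sentence correct.

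A reader might infer that the table must come out empty. The documents do not establish that. The end of the phase is not defined, Section 3 lists vaccination and follow-up as separate parts of a subject's time in the study, and Table 2 has separate blocks of rows for vaccination and follow-up visits. Empty is the result of one reading; under another, 29 of 86 days remain. Every reading in the table above fails the endpoint. A further possibility is that the timing refers to when results are written up. The sentence attaches it to the event, and on that meaning too it would need rewording and would still state no 30-day window.

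A reader might also infer that early unsolicited events vanish from the safety report. They do not: the first bullet of Section 10.4.2 still counts them for seven days, pooled with solicited events. That falls short of the 30-day endpoint, but it is not nothing.

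Finally, Section 8.1.3 classes as unsolicited "solicited symptoms which begin after the seven-day follow-up period for solicited symptoms", and a reader might infer that an injection-site reaction to Dose 2 on Day 28 becomes an unsolicited event of Dose 1. Section 8.1.2 rules this out: the reaction lies within the seven-day solicited period of Dose 2 and is a solicited event of that dose. The high pain rate in Table 1 therefore says nothing about misclassified unsolicited events.

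On the overlap, the instructions at Visits 8 and 14 already have unsolicited events recorded relative to the last dose given, and a counting rule alone could be left to a statistical analysis plan. Both points stand, so the overlap is secondary.

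**Conclusion.** The point holds. The restriction in Section 10.4.2 contradicts the second co-primary endpoint and makes the requested per-dose table unobtainable. Taken literally, it removes between 57 of 86 nominal follow-up days (86 − 29, phase ending at Dose 3) and all 86 (phase ending at Day 86 or later). Dose 1 is lost entirely and Dose 2 almost entirely, whichever reading is taken.

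These counts rest on the nominal schedule and on events being reported near their onset. They are days of follow-up; the protocol gives no basis for translating them into numbers of events. No type I error rate, power or sample size depends on the point. The window overlap is real but minor, and is best settled in the same edit.

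**What to change.** In the third bullet of Protocol Section 10.4.2, replace the reference to the Vaccination Phase by: *with onset from the day of vaccination through 29 days after each vaccination, tabulated per group and vaccine dose, and overall per subject*. Then add two short rules:

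- In the per-dose table each event is counted once, under the most recent dose before or at its onset. This agrees with the recording instructions at Visits 8 and 14. It leaves the 30-day endpoint unchanged and only settles where an event in the overlap is shown.
- Events with onset outside every 30-day window are listed separately, both those after Dose 3 up to the final visit and those in a gap between widely spaced doses.

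The cost is one reworded sentence and two added ones. Onset dates are already collected, so no data, visits or procedures change. Any statistical analysis plan should be checked for the same restriction.

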**Clinical Laboratory parameters**

Hematological and biochemical laboratory parameters will be measured at specific time points during the study. Clinically relevant abnormal values will be tabulated.

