## Eliciting and documenting adverse events

### Adverse event definition

An AE is any untoward medical occurrence in a study volunteer, temporally associated with the use of a test article, whether or not considered related to the test article. An AE can therefore be any unfavorable and unintended sign (including an abnormal laboratory finding), symptom, or disease (new or exacerbated) temporally associated with the use of a test article whether or not it is considered to be study related.

Examples of an AE include:

- Exacerbation of a chronic or intermittent pre-existing condition including either an increase in frequency and/or intensity of the condition.
- New conditions detected or diagnosed after investigational product administration even though it may have been present prior to the start of the study.
- Signs, symptoms, or the clinical sequelae of a suspected overdose of either investigational product or a concurrent medication (overdose per se should not be reported as an AE/SAE).
- Signs, symptoms temporally associated with vaccine administration.

AEs may include pre- or post-treatment events that occur as a result of protocol-mandated procedures (i.e., invasive procedures, modification of subject’s previous therapeutic regimen). Pre-existing conditions or signs and/or symptoms present in a subject prior to the start of the study (i.e. prior to the first study procedure) as well as any that are not recognized at study entry but are recognized during the study period, should be recorded in the medical history section of the subject’s CRF. Adverse events that occur after informed consent is obtained, but prior to vaccination, will be documented the Medical History form within the participant's CRF. Anticipated day-to-day fluctuations of pre-existing conditions, including disease under study, that do not represent a clinically significant exacerbation need not be considered adverse events. Adverse events should be documented in terms of medical diagnosis(ses) when possible. When this is not possible, the adverse event should be documented in terms of signs and symptoms observed by the investigator or reported by the participant at each study visit.

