## Assessment of intensity

Intensity of the solicited adverse events should be assessed as described in Tables 5-7. Grading of hematological and biochemical laboratory adverse events are in Table 8-9.

Table 5: Intensity grading of local solicited adverse events

| **Adverse event** | **Intensity grade** | **Intensity** |
| --- | --- | --- |
| Pain at injection site | 0 | Absent |
|  | 1 | Mild pain not interfering with function |
|  | 2 | Moderate pain; pain interfering with function but not interfering with activities of daily living (ADL) |
|  | 3 | Severe Pain; pain that severely interferes with ADL |
| Erythema at injection site | | Record greatest surface diameter in mm (see Table 9 ) |
| Swelling at injection site | | Record greatest surface diameter in mm (see Table 9 ) |

Intensity of the general adverse events should be assessed as described in Table 8.

Table 6: Intensity grading of general solicited adverse events

| **Adverse event** | **Intensity grade** | **Intensity** |
| --- | --- | --- |
| Fever (oral temperature  37.5C or 99.5F). | | Record oral temperature in °C/F (see Table ) |
| Headache | 0 | Normal |
|  | 1 | Headache which is easily tolerated |
|  | 2 | Headache that interferes with normal activity |
|  | 3 | Headache that prevents normal activity |
| Fatigue | 0 | Normal |
|  | 1 | Fatigue which is easily tolerated |
|  | 2 | Fatigue that interferes with normal activity |
|  | 3 | Fatigue that prevents normal activity |
| Gastrointestinal | 0 | Normal |
| (*Nausea)* | 1 | GI symptoms which are easily tolerated |
|  | 2 | GI symptoms that interfere with normal activity |
|  | 3 | GI symptoms that prevent normal activity |
| Malaise | 0 | Normal |
|  | 1 | Malaise which is easily tolerated |
|  | 2 | Malaise that interferes with normal activity |
|  | 3 | Malaise that prevents normal activity |
| Myalgia | 0 | Normal |
|  | 1 | Myalgia which is easily tolerated |
|  | 2 | Myalgia that interferes with normal activity |
|  | 3 | Myalgia that prevents normal activity |
| Joint pain | 0 | Normal |
| (> 1 joint) | 1 | Joint pain which is easily tolerated |
|  | 2 | Joint pain that interferes with normal activity |
|  | 3 | Joint pain that prevents normal activity |

Table 7: Intensity grading assigned

| Erythema at injection site | 0 | 0 mm |
| --- | --- | --- |
|  | 1 | > 0 - 20 mm |
|  | 2 | > 20 - 50 mm |
|  | 3 | > 50 mm |
| Swelling at injection site | 0 | 0 mm |
|  | 1 | > 0 - 20 mm |
|  | 2 | > 20 - 50 mm |

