Abnormal laboratory findings (e.g., clinical chemistry, hematology, urinalysis) or other abnormal assessments (e.g. blood film) that are judged by the investigator to be clinically significant will be recorded as AEs or SAEs if they meet the definition of an AE, as defined in Section 8.1 or SAE, as defined in Section 8.5. Clinically significant abnormal laboratory findings or other abnormal assessments that are detected during the study or are present at baseline and significantly worsen following the start of the study will be reported as AEs or SAEs. However, clinically significant abnormal laboratory findings or other abnormal assessments that are associated with the disease being studied, unless judged by the investigator as more severe than expected for the subject’s condition, or that are present or detected at the start of the study and do not worsen, will not be reported as AEs or SAEs.

The investigator will exercise his or her medical and scientific judgment in deciding whether an abnormal laboratory finding or other abnormal assessment is clinically significant.

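### The stated laboratory safety analysis covers only abnormal values judged clinically relevant, an undefined term, so out-of-range values judged not relevant may go unreported

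*Protocol*

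**What the plan says.** Section 5.5 schedules a full blood count, creatinine, AST and ALT on Days 0, 7, 28, 35, 56, 63 and 112. Tables 8 and 9 give reference ranges and critical values for these parameters. The laboratory analysis in section 10.4.2 notes that parameters will be measured at specific time points, and then says: "Clinically relevant abnormal values will be tabulated".

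Three other places bear on the same values:

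- Section 8.1.1 gives the general definition: "An AE can therefore be any unfavorable and unintended sign (including an abnormal laboratory finding), symptom, or disease". It also requires adverse events within 30 days of each dose to be recorded "irrespective of severity or whether or not they are considered vaccination-related".
- Section 8.3 narrows this for laboratory findings. It covers those "that are judged by the investigator to be clinically significant will be recorded as AEs or SAEs if they meet the definition of an AE". The criterion is judgement: "The investigator will exercise his or her medical and scientific judgment in deciding whether an abnormal laboratory finding or other abnormal assessment is clinically significant".
- Section 8.2 states: "Grading of hematological and biochemical laboratory adverse events are in Table 8-9".

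**The concern.** Two filters stand between an out-of-range value and the safety report. One, in section 8.3, decides whether the value is recorded as an adverse event. The other, in section 10.4.2, decides whether it enters the laboratory table. Both rest on judgement without a numeric anchor. They use different words, and nothing says whether *clinically relevant* and *clinically significant* mean the same thing. A value that fails both has no stated route into the results.

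What is at stake is the laboratory part of the safety objective. Laboratory parameters are not listed among the co-primary endpoints in section 10.2; they reach those endpoints only when recorded as unsolicited or serious adverse events. The table in section 10.4.2 is thus the one place where the protocol undertakes to show laboratory data as such. If its content depends on case-by-case judgement, another team with the same data could produce a different table, and mild but repeated abnormalities could be left out of it.

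**Working it through.** The protocol gives no figure for laboratory safety, so there is none to reproduce. The check is a reading of the sections together, followed by an illustration of scale.

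**Step 1. Follow one value through the rules.** Take an ALT of 50 U/L on Day 35. Table 8 gives a reference range of 0 to 35 and a critical value above 75, so the result is abnormal but not critical.

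- Section 8.1.1: it *can* be an adverse event.
- Section 8.3: it is recorded as one only if judged clinically significant.
- Section 10.4.2: it is tabulated if clinically relevant, with no definition.
- Section 8.2 points to Tables 8 and 9 for grades, but those tables hold only reference ranges and critical values. They supply no graded threshold that could stand in for the missing definition.

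If the answer under both section 8.3 and section 10.4.2 is no, the value is in neither place. The same holds for a male haemoglobin between 8 and 13 g/dL (Table 9).

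**Step 2. Background frequency.** Section 1.3.2 describes an earlier study in 255 adults in western Kenya, in three groups. Mild anaemia occurred in 10 RTS,S/AS01B, 3 RTS,S/AS02A and 6 control recipients, and raised ALT in 1, 7 and 3. Group sizes are not given. I assume 255/3 = 85 per group, and show 80 to 90. The sums below are upper limits, because a volunteer with both findings would be counted twice.

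| | AS01B | Control |
|---|---|---|
| Mild anaemia | 10/85 = 11.8% | 6/85 = 7.1% |
| Raised ALT | 1/85 = 1.2% | 3/85 = 3.5% |
| Either, at most | 11/85 = 12.9% (12.2% to 13.8%) | 9/85 = 10.6% (10.0% to 11.3%) |

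Applied to 20 volunteers, the last row is 20 × 11/85 = 2.6 against 20 × 9/85 = 2.1. Fisher's exact test gives p = 0.81 for 11 against 9, and p = 0.43 for anaemia alone (10 against 6). Neither changes materially for 80 to 90 per group. These are rates of background abnormality and show no difference between vaccine and control.

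**Step 3. Effect of the filter.** Let p be the frequency of mild anaemia (10/85) and q the share of such cases judged relevant. The expected number tabulated among 20 vaccinees is 20pq. The chance that the table shows at least one is 1 − (1 − pq)^20.

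| q | Expected of 20 | Chance of at least one |
|---|---|---|
| 1 | 2.4 | 0.92 |
| 0.5 | 1.2 | 0.70 |
| 0.25 | 0.6 | 0.45 |
| 0.1 | 0.2 | 0.21 |
| 0 | 0 | 0 |

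For 80 to 90 per group, the first row becomes 2.5 to 2.2 expected and 0.93 to 0.91. The protocol gives no value for q, so the content of the table is not fixed by the plan.

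**Step 4. Is a comparison with baseline feasible?** Section 4.3 excludes volunteers whose screening ALT or creatinine is above range, or whose haemoglobin, platelets or white cells are below it. Later out-of-range values of these kinds will mostly be new since screening, so a shift from Day 0 would be easy to read.

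**The case against.** The strongest reply is that out-of-range listings and shift tables are ordinary content of a statistical analysis plan, which is not at hand, and that section 10.4.2 does not say that nothing else will be shown. That stands as far as it goes: the protocol excludes no further summary, and the absence of a shift table alone would be no finding. But the protocol is not silent. It names one laboratory analysis and builds an undefined filter into it.

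A second reply is that judgements are made observer-blind (section 5.4, Method of blinding), that clinical significance is not the same as severity, and that a mild value can be judged significant and kept. This also stands. The loss is in sensitivity and reproducibility, and need not favour either arm.

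A third is that with 20 against 10 volunteers a mild shift could not be separated from control. The 95% interval for a difference in mean change has a half-width of about 2.05 × √(1/20 + 1/10) = 0.79 standard deviations. True, and the sample size section itself expects a descriptive safety analysis. The case is for complete description, not for a test.

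Three stronger readings are tempting, and the documents do not support them:

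- *Sections 8.1.1 and 8.3 contradict each other.* Section 8.1.1 says a laboratory finding can be an adverse event, and section 8.3 refers back to that definition. This is a general definition with a narrower recording rule.
- *Baseline values are not used.* Section 8.3 counts abnormalities present at baseline that significantly worsen, and leaves out those present at the start that do not. What is missing is a stated shift summary.
- *Vaccine-caused shifts would disappear.* No such shift is shown. The earlier study tested a different antigen, and its control group had nearly as many abnormalities.

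**Conclusion.** The point holds in limited form. The one laboratory analysis that the protocol states depends on a judgement-based term that is undefined and unlinked to the term governing laboratory adverse events. Out-of-range values judged not relevant may therefore go unreported in both places.

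The size cannot be fixed from the protocol, because the share judged relevant is unknown. For a finding with a background frequency of 11.8%, the chance of seeing any case among 20 vaccinees lies anywhere from 0 to 0.92. This rests on the assumed 85 per group, on carrying the earlier study's frequency over to this trial, and on independence between volunteers. It illustrates reliance on the filter and is no estimate of harm missed. The change is worth making because the data are already collected and bear on the primary safety objective.

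**What to change.** In section 10.4.2, replace the sentence on clinically relevant values with a commitment to tabulate, by group and visit, every value outside the reference ranges in Tables 8 and 9, with a descriptive shift from Day 0. Mean change from Day 0 with a 95% confidence interval may be added, on the understanding that it will be imprecise at 20 against 10.

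Keep the investigator's judgement in section 8.3 solely as the rule for recording a laboratory adverse event, and use one term for it in sections 8.3 and 10.4.2.

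The cost is a few more descriptive tables and a small wording change. No extra blood, visits or data collection are needed.
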